### Dose reduction in case of adverse events

The investigator should determine if an adverse event is related to the study drug. Adverse events (AE) considered at least possibly related to study drug may require a dose reduction, a temporary hold (up to 7 days), or permanent discontinuation. Dose modifications should be based on the NCI CTCAE (version 4). Dose reduction for Grade 1 AEs is not required. Dose reduction for Grade 2 events should be considered only when the AE is judged by the investigator to be clinically intolerable. For Grade 3 and 4 AEs, the dose modification of study drug should follow the Dose Reduction Guidelines in the Tables 2 and 3 below. Dose modification for Grade 3 or 4 diarrhoea should follow the guidelines in Table 4 below.

**Table 2 Tab2:** General dose reduction guidelines

Grade I	Continue study treatment at same dose; monitor and treat as clinically indicated.
Grade II	Continue study treatment at same dose; monitor and treat as clinically indicated.
Grade III	Step 1. Interrupt study drug until toxicity reduced to ≤Grade 1. Step 2. Restart study treatment at same dose or lower dose at discretion of investigator
Grade IV	Step 1. Interrupt study drug until toxicity reduced to ≤Grade 2. Step 2. Restart study treatment at lower dose level.

**Table 3 Tab3:** Dose level dose

Dose level	Dose
0	1 g BD.
-1	500 mg BD
-2	Discontinuation

**Table 4 Tab4:** Dose reduction for specific toxicity: diarrhoea

Grade I	No action required.
Grade II	Concomitant anti-diarrhoeal agents may initially be administered without dose reduction. If Grade 2 diarrhoea persists, dose reduction should occur as per Table 2. Supportive care regimen should follow local standard of care.
Grade III	Dose reduction should occur as per Table 2.
Grade IV	Dose reduction should occur as per Table 2.

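### Persistent Grade 2 diarrhoea has conflicting dose instructions: Table 4 sends it to Table 2 for a reduction, Table 2 keeps the dose unchanged, and the running text applies a different test

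*Protocol article*

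**What the plan says.** All the dose-modification rules are in the section Dose reduction in case of adverse events.

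- **Running text, Grade 2 events in general:** "Dose reduction for Grade 2 events should be considered only when the AE is judged by the investigator to be clinically intolerable".
- **Running text, where to look for diarrhoea:** "Dose modification for Grade 3 or 4 diarrhoea should follow the guidelines in Table 4 below". It does not send Grade 2 diarrhoea to Table 4.
- **Table 2 (general guidelines), Grade II row:** "Continue study treatment at same dose; monitor and treat as clinically indicated". The Grade I row has the same wording.
- **Table 4 (diarrhoea), Grade II row:** anti-diarrhoeal agents may be given first without a reduction, and then "If Grade 2 diarrhoea persists, dose reduction should occur as per Table 2".
- **Table 3:** level 0 is 1 g twice daily, level -1 is 500 mg twice daily, and level -2 is discontinuation.

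The section Per protocol analysis bases the primary endpoint on men with at least 21 days of study drug at 1.5–2.0 g daily and no interruption in the last 7 days before prostatectomy. Intention-to-treat is a secondary analysis.

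**The concern.** Table 4 orders a dose reduction and names Table 2 as the place that says how. Table 2 has no reduction for that grade. A site that follows the cross-reference arrives at an instruction to leave the dose alone. A site that reads the running text applies another test again, tolerability instead of persistence.

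Two things are at stake. The first is consistent handling: the Background names mild gastrointestinal discomfort with diarrhoea as the most common side effect of metformin, so a diarrhoea rule ought to be unambiguous. The second is who enters the primary analysis. That analysis is restricted by dose received, so a site's reading of an ambiguous dose rule can affect whether a man is counted. If such losses occur, one would expect them more often on metformin than on placebo, which would make the exclusion related to treatment.

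**Working it through.** No sample-size figure enters the main point, so the check is a comparison of the text, followed by simple arithmetic on dose and days.

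**1. Persistent Grade 2 diarrhoea, line by line**

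| Source | Condition | Action |
|---|---|---|
| Table 4, Grade II | diarrhoea persists | reduce, by reference to Table 2 |
| Table 2, Grade II | any Grade II event | same dose |
| Running text | Grade 2 event judged intolerable | reduction may be considered |
| Running text | Grade 2 event not judged intolerable | no reduction |

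Take a man whose Grade 2 diarrhoea persists but is tolerable. Table 4 says reduce; Table 2 and the running text say do not. If the same diarrhoea is judged intolerable, Table 4 says reduce, the running text says consider it, and Table 2 says do not. In neither case do the three agree.

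**2. What a reduction means for the per-protocol dose band**

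One step down from level 0 is level -1: 2 x 500 mg = 1.0 g daily. The band starts at 1.5 g daily, and Table 3 has no level between 1.0 and 2.0 g daily. Days at level -1 therefore do not count towards the 21.

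**3. How much room there is**

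Under Dosing regimen, days 1–2 are at 0.5 g and days 3–4 at 1.0 g daily, both below the band. In-range dosing starts on day 5, so 21 in-range days are first complete at the end of day 25 (days 5 to 25).

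- Surgery around day 28, last dosing day 27 or 28: 27 - 4 = 23 or 28 - 4 = 24 in-range days, so 2 or 3 days to spare.
- Four weeks counted from day 5: 28 in-range days, so 7 to spare.
- Surgery a week later, last dosing day 34 or 35: 30 or 31 in-range days, so 9 or 10 to spare.

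A man reduced from day 26 onwards with no earlier shortfall can stay evaluable, because a reduction is not an interruption. On the day-28 reading, a reduction that starts earlier and lasts more than 2 or 3 days takes him out of the per-protocol population.

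**4. Whether a number of men can be stated**

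The Background's figure above 10% is for mild discomfort. For Grade 1 diarrhoea the running text, Table 2 and Table 4 all agree that the dose stays the same, so mild cases do not meet the conflict. Neither the Background nor IMP risks gives a rate for Grade 2, persistent Grade 2 or worse. The number of men affected cannot be derived.

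For scale only, suppose that 5 metformin men were lost (10% of 50, an assumption). For Scenario 1 of Table 6 (difference 15, SD 35, two-sided alpha 0.20), the non-centrality is (15/35) x sqrt(n1 x n2/(n1 + n2)). At 50 and 50 it is 0.4286 x 5.000 = 2.143, and power is 80.3%, in line with the plan's 80%. At 45 and 50 it is 0.4286 x 4.867 = 2.086, and power is 78.7%.

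**The case against.** The best defence is that a disease-specific table overrides a general one, so Table 4 governs diarrhoea. That would work if Table 4 stated the action itself. It hands the action back to Table 2, so the override ends in the row that it was meant to override. The cross-reference may be a slip, but the article does not say so.

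A second defence is that the running text sends only Grade 3 and 4 events to Tables 2 and 3 and deals with Grade 2 itself, so the intolerability clause is an exception to Table 2's default. That is a fair reading and softens the difference between the running text and Table 2. It leaves Table 4 against Table 2 untouched.

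Several stronger readings are tempting, and the objections to them stand:

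- **Restart thresholds.** After Grade III, Table 2 says "Interrupt study drug until toxicity reduced to ≤Grade 1"; after Grade IV, "Interrupt study drug until toxicity reduced to ≤Grade 2". A reader might infer a contradiction because the looser threshold follows the more severe event. These are two rows of one table for different events, and Grade IV carries a compulsory lower dose ("Restart study treatment at lower dose level"). The order is unexplained and may be deliberate.
- **Grade III diarrhoea.** Table 4 says that reduction should occur under Table 2, whereas Table 2 says "Restart study treatment at same dose or lower dose at discretion of investigator". A reader might infer a second contradiction. The wording is loose, but it leads to one row with stated steps, including the discretion.
- **Lost power.** A reader might take 10% of 50 men as affected, or even remove 5 men from each arm. The 10% refers to mild events, and the article gives no basis for losing placebo men to metformin diarrhoea.
- **Evaluability.** A reader might infer that the line followed always settles whether a man is in the primary analysis. It does not for a man who already has 21 days in range.

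**Conclusion.** The point holds for persistent Grade 2 diarrhoea. Table 4 and the Grade II row of Table 2 cannot both be followed, and the running text adds a different criterion and leaves Grade 2 diarrhoea outside the stated scope of Table 4. The text is complete and legible, so this is not a fault of extraction. Nor is it detail that an article would leave to the full protocol, because the article prints the rules and they disagree.

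The consequence for the analysis is possible but of unknown size. It rests on level -1 being 1.0 g daily, on the 1.5–2.0 g band being applied as written, and on the reduction coming before 21 days in range have been reached. No power loss is claimed. This is a wording error that should be corrected, not evidence that the primary result is at risk. The Grade III wording and the restart thresholds are secondary matters for alignment and confirmation.

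**What to change.** The clinical team should reconcile the running text, Table 2 and Table 4 so that Grade 2 events in general, and persistent Grade 2 diarrhoea in particular, each have one stated action, and so that the running text says which grades of diarrhoea Table 4 covers.

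In the same amendment:

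- align the Grade III wording of Table 4 with the discretion given in Table 2;
- confirm that the Grade III and Grade IV restart thresholds are as intended.

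Which dose or threshold applies is for the clinical team, and none is proposed here. The cost is an amendment to the wording and, as the trial is already open at two sites, a notice to both. Sample size and analysis do not change.

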### IMP risks

As Metformin is a licensed drug the reference document will be the Medley Pharma laboratories Summary of Product Characteristics (SmPC). The very common unwanted effects (less than or equal to 1 in 10) are gastrointestinal symptoms such as nausea, vomiting, diarrhoea, abdominal pain and loss of appetite.

Lactic acidosis is a rare, but serious, metabolic complication that can occur due to metformin accumulation. Reported cases of lactic acidosis in patients on metformin have occurred primarily in diabetic patients with significant renal failure. The incidence of lactic acidosis can and should be reduced by assessing other associated risk factors such as poorly controlled diabetes, ketosis, prolonged fasting, excessive alcohol intake, hepatic insufficiency and any condition associated with hypoxia. For full details please refer to the SmPC.

### Drug accountability

The pharmacy will keep accountability records for reconciliation purposes. These should be used to record the identification of the subject to whom the investigational product was dispensed, the date, batch number, expiry date and quantity of the investigational product dispensed and the quantity of the investigational product unused/returned by the subject. Participants will be asked to return all packaging to pharmacy for accountability. Any excess or unused drug will be collected by the trial team, retained for verification by the local Clinical Research Associate (CRA) and destroyed by Guy’s Hospital Pharmacy in accordance with local requirements when authorised to do so. Disposal of unused investigational medicinal product (IMP) is only permitted with sponsor authorisation.

### Storage of IMP

This IMP does not require any special storage conditions. IMP should be handled and stored safely and properly in accordance with the drug label. Patients will be instructed to store study drug at room temperature out of reach of children.

### Subject compliance

Trial subjects will undergo a compliance evaluation at their Study week 3 (+/− 2 days) visit. This will consist of reviewing a medication diary given at enrolment and a verbal questioning about drug compliance.

### Concomitant medication

For management of concomitant therapies, please refer to the SMPC.

### Participant timeline

Please see below Fig. 1 for the trial schema and Table 5 for the trial flow chart.

**Fig. 1 Fig1:**
[figure not shown]
Trial Schema

**Table 5 Tab5:** Trial Flow Chart

Phase	Screening	Pre-surgery Treatment			Surgery	Post-surgery
Time point	≤14 days before baseline	Baseline Day 1 of treatment	Day 21 (+/- 2 days)	Day 28 (+/- 1 week) prior to surgery	Day 28 (+/- 1 week)	8-10^f^ weeks post-op
Informed consent	x					
Eligibility review	x	x				
Randomisation		x				
Medical History^a^	x					
Demographics	x					
Physical Exam	x	x	x	x		x
Vital signs^b^	x		x	x		x
ECOG PS	x	x	x	x		x
Height	x					
Weight	x			x		x
Waist/Hip ratio	x			x		x
Haematology	x		x	x		x
Biochemistry^c^	x		x	x		x
Fasting Glucose/Lipids	x			x		
PSA and Testosterone	x			x		x
HbA1c	x					
Whole blood and Serum save^d^	X			X		
Study Drug Administration		x	x	x		
Medication review	x	x	x	x		x
Compliance evaluation (diary and verbal)			x	x		
Adverse events (CTCAE v4)^e^		x	x	x		x
Paraffin embedded tissue sent to laboratory	x				x	
Prostatectomy					x	
MRI safety assessment^g^	x					
^18^F Choline PET/MRI^g^	x			X^e^		

^a^Full medical history, including history other disease, active or resolved, concomitant illnesses and cancer diagnosis

^b^Blood pressure, pulse rate and oxygen saturation, BM

^c^Renal profile, liver function tests, bone profile

^d^To be taken at selected sites only and according to the Trial specific SOP

^e^Clavien Dindo assessment to be completed at 8-10 weeks post operatively

^f^This review will coincide with routine post-operative review

^g^Only for the 5 subjects participating in the exploratory PET-MRI group

### Recruitment

Patients will be identified in multi-disciplinary team meetings or in out-patient clinics by the clinical team. Only patients with adequate diagnostic prostate biopsy specimen available for baseline immunohistochemistry will be approached for participation in this study. Assessment of this will be undertaken by an experienced uro-pathologist present during multi-disciplinary team meetings. Patients will be selected to be approached for recruitment in to either the sub study or the main study, depending on whether the criteria for the sub study are fulfilled. Patients approached about the sub study, will be able to opt for enrolment in to the main study should they wish. Once all five patients are recruited to the sub study, all subsequent patients will be approached only about the main study.

## Methods: Assignment of interventions

### Randomisation

Patients will be randomised using block randomisation with randomly varying block sizes. Randomisation will be performed via a web based independent randomisation service, hosted at the UKCRC registered KCTU. Researchers will access the system via http://www.ctu.co.uk and will login with individual usernames and passwords. When a patient is confirmed as eligible and consenting, their study ID, initials, and date of birth will be entered into the system, along with any relevant stratification information, and the patient will be randomised to active or placebo medication. The system will auto-generate confirmation emails to pharmacy advising of the trial arm to be dispensed. A blinded confirmation email will be generated to the rest of the research team.

### Emergency code break

Investigators and patients will remain blinded to the treatment allocation throughout the trial. Unblinding should not normally be necessary as serious side-effects should be dealt with on the assumption that the patient is on active metformin treatment. Study medication should be omitted rather than unblinded. Request for unblinding should be directed to local pharmacy during office hours. In case of emergency un-blinding being necessary out of hours, the on call pharmacist should be contacted. Contact details for individual sites will be provided on site specific emergency contact list.

### Withdrawal of patients

Participants have the right to withdraw from the study at any time for any reason. The investigator also has the right to withdraw patients from the study drug in the event of inter-current illness, AEs, SAE’s, SUSAR’s, protocol violations, administrative reasons or other reasons. It is understood by all concerned that an excessive rate of withdrawals can render the study un-interpretable; therefore, unnecessary withdrawal of patients should be avoided. Should a patient decide to withdraw from the study, all efforts will be made to report the reason for withdrawal as thoroughly as possible. Should a patient withdraw from study drug only, efforts will be made to continue to obtain follow-up data, with the permission of the patient.

Participants who wish to withdraw from IMP will be asked to confirm whether they are still willing to provide the following.trial specific data at their follow up visit

Patients who interrupt study drug for greater than 7 days, without the direction from their treating doctors, will be considered as non-compliant and will be discontinued from the study. These patients will be included in the safety assessments. They will be included in the pharmacodynamic, efficacy and safety assessments only if they received at least 21 days of treatment.

Treatment with study drug should be discontinued if it is considered to be in the best interest of the patient. Reasons for treatment discontinuation include:Disease progressionOccurrence of intolerable side effectsPatient withdrawal of consent or non-compliance.

Patients discontinued from the study for reasons unrelated to therapy, such as non-compliance, ineligibility or withdrawal of consent will be considered drop-outs. All of these patients are still evaluable for toxicity. Any subjects who withdraw prior to completing treatment will be replaced until 90 subjects in each of the randomized study arms have completed treatment.

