Radiological assessment: In a subgroup of 5 patients with MRI positive disease: ^18^ F Choline PET/MRI, which will be performed after 21+/− 2 days of metformin and prior to prostatectomy. A time point prior to 28 days is chosen to allow radiological assessment to be scheduled without interfering with surgery scheduling.
A pre-operative surgical visit should occur prior to surgery, as per standard of care and local policies.

Study week 4 (+/− 1 week) – prostatectomy:

Patients will undergo prostatectomy. This will occur at the end of week 4 (+/− 1 week). Study drug treatment will continue up until the evening before surgery until the patient is nil by mouth (as per local guidelines). In the events patients undergo surgery beyond 4 weeks from randomisation; study drug will be continued for an additional 1 week. Surgery should occur as per local policies.If clinically necessary, surgery can be brought forward or not performed (this should be discussed with the Chief Investigator). The case should be presented to a multidisciplinary team meeting before any other non-surgical treatment is given. These patients will not be included in the analysis as, in the absence of surgery, it will not be possible to assess for post-treatment tissue markers.
Tissue Collection: Formalin Fixed Paraffin Embedded tissue will be taken from the radical prostatectomy specimen

Follow up 8–10 weeks post operativelyClinical assessments:Symptoms directed physical examination, including ECOG performance status, weight, waist/hip ratio and vital signsMedications reviewAdverse events and complete Clavien Dindo assessment
Laboratory determinations: Blood tests taken within 2 days of post-operative visit for other purposes can be used as part of the post-operative visit: FBC, renal function, LFT, bone profile, PSA, testosterone.

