### Dosing regimen

In order to limit gastrointestinal side effects patients will be instructed to take study drug at doses increasing from:500 mg once a day (day 1–2)500 mg twice a day (day 3–4)1 g twice a day from day 5 onwards for 4 weeks until prostatectomy +/− one week

Study drug will be continued until the evening prior to surgery. Placebo will be dose escalated in the same way. Participants will be given these instructions verbally as well as written instructions at the start of their medication compliance diary.

Study drug doses should ideally be taken at the same time each day. Missed doses of the study drug may be taken later, provided that the time of dosing is at least 6 h before the next scheduled dose. If dosing is missed for one day for any reason, double-dosing should not occur the following day. Acute alcohol intoxication can increase the likelihood of the rare, but serious adverse event of lactic acidosis. Therefore, all participants will be advised to avoid alcohol for the duration of the trial. Patients participating in the non-randomised 18F PET/MRI cohort will receive metformin, which will be dose escalated as outlined above. All dose modifications and duration of treatment will be identical to the randomized cohort.

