### Safety analysis

The safety population is defined as all randomised patients who received at least 1 dose or partial dose of study drug. The safety population will be analysed by treatment arm as treated. The safety population will be used to conduct safety analyses.

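### The withdrawal rule ties safety inclusion of men who stop study drug themselves to 21 days of treatment, against the one-dose safety population

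*Protocol article*

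**What the plan says.** The rule stands in the protocol article under Withdrawal of patients. It covers men who interrupt study drug for more than 7 days without direction from their doctors; they "will be considered as non-compliant and will be discontinued from the study". Four statements then bear on whether such a man counts for safety:

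- Withdrawal of patients, next sentence: "These patients will be included in the safety assessments".
- Withdrawal of patients, the sentence after that: "They will be included in the pharmacodynamic, efficacy and safety assessments only if they received at least 21 days of treatment".
- Withdrawal of patients, last paragraph, on drop-outs, with non-compliance named among the reasons: "All of these patients are still evaluable for toxicity".
- Safety analysis: "The safety population is defined as all randomised patients who received at least 1 dose or partial dose of study drug", and "The safety population will be used to conduct safety analyses".

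**The concern.** The second statement makes 21 days of treatment a necessary condition for entering the safety assessments. The other three set no such minimum. For a man who took at least one dose but had fewer than 21 days of drug, the document gives two incompatible answers.

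Safety of metformin in men without diabetes is a secondary objective in Table 1. The Background section names gastrointestinal discomfort as the drug's most common side effect, so some men may stop taking tablets because they do not tolerate them. If the 21-day sentence were followed, early stoppers would leave the safety set and toxicity could be understated. If the Safety analysis section were followed, they would stay in.

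**Working it through.** **Side by side.** Take a randomised man who takes drug for 10 days and then stops on his own for more than 7 days.

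| Statement | Minimum exposure | Counted for safety? |
|---|---|---|
| Withdrawal of patients, first safety sentence | none | in |
| Withdrawal of patients, 21-day sentence | 21 days | **out** |
| Withdrawal of patients, drop-out paragraph | none | in |
| Safety analysis | one dose or partial dose | in |

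Three statements keep him and one removes him. Nothing in the text ranks the 21-day sentence above or below the others. Elsewhere in the article, a 21-day minimum appears only among the criteria for the per-protocol analysis of the primary endpoint (Trial design; Per protocol analysis), which suggests that safety was added to this sentence by mistake.

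**Who can fall into the conflict.** The inputs are the gap and the course length.

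- Gap: more than 7 days, so at least 8 whole days.
- Course of 28 days: the nominal four weeks.
- Course of 32 days: Dosing regimen read literally, with full dose "twice a day from day 5 onwards for 4 weeks until prostatectomy", gives 4 escalation days + 28 = 32.
- Course of 35 days: under Interventions, if surgery falls beyond four weeks, "study drug will be continued for an additional 1 week", so 28 + 7 = 35.
- Course of 29 days: included because it is the shortest on which 21 days can remain.

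*Most drug days that can remain* = course length L − 8:

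- 28 − 8 = 20
- 29 − 8 = 21
- 32 − 8 = 24
- 35 − 8 = 27

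*If the man does not restart*, which fits the rule that he is discontinued, a first missed day s leaves s − 1 days of drug. At least one day of drug requires s ≥ 2, and a gap of at least 8 days within the course requires s ≤ L − 7. He is caught when s − 1 < 21, that is, when s ≤ 21.

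| L (days) | Possible first missed days | Caught (fewer than 21 days) | Escape (21 days or more) |
|---|---|---|---|
| 28 | 2 to 21 (20) | 20 | 0 |
| 29 | 2 to 22 (21) | 20 | 1 |
| 32 | 2 to 25 (24) | 20 | 4 |
| 35 | 2 to 28 (27) | 20 | 7 |

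Table 5 also allows surgery up to a week early. On a course of 21 to 27 days, at most 21 − 8 = 13 to 27 − 8 = 19 drug days remain, so every such man who took a dose is caught.

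These are counts of possible start days, not of patients. They show that the conflict covers most or all of the possible timings. They say nothing about how often men interrupt treatment, for which the document gives no figure.

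**The case against.** The strongest reply is that the two adjacent sentences can be read together: every such man counts for safety, and with 21 days he counts for all three kinds of assessment. On the stricter reading, the second sentence would cancel the one directly before it. The Safety analysis section, which defines the population actually used, sides with the inclusive reading, so an analyst would have to override it to exclude anyone. This is fair as an account of the intent. It does not change the wording, which lists safety under an *only if* condition.

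A second reply concerns harm. Intolerable side effects are listed as a separate reason for stopping treatment, distinct from non-compliance. The drop-out paragraph covers discontinuations unrelated to therapy, so it does not clearly protect men who stop because of intolerance. This part stands, and it narrows the likely harm. Even so, the non-compliance rule turns on the length of the gap and the absence of a doctor's direction, not on the motive. A man who quietly stops because of diarrhoea meets it.

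Third, the start-day counts give no rate or bias. That is correct, and none is claimed from them.

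Finally, the same sentence admits men to the pharmacodynamic assessments on 21 days alone, whereas Per protocol analysis also sets a dose range and requires uninterrupted drug over the last 7 days. That is a separate point, which the change below does not settle.

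**Conclusion.** The text is wrong as written, and the point is minor. One sentence under Withdrawal of patients sets a 21-day condition on safety inclusion that conflicts with two other statements in the same section and with the Safety analysis section.

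The conflict is confined to men with at least one dose, fewer than 21 days of drug and a self-directed interruption of more than 7 days. Within that kind of interruption, it catches every man who took a dose on courses of up to 28 days. On longer courses without a restart, it catches all whose first missed day is day 21 or earlier. Doctor-directed holds of up to 7 days, under Dose reduction in case of adverse events, are outside it. The safety condition does not bear on the primary endpoint.

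The conclusion that toxicity could be understated rests on two assumptions: that someone applies the 21-day sentence, and that some early stoppers stop because of side effects. The number of men affected cannot be estimated from the document.

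**What to change.** In the 21-day sentence under Withdrawal of patients, delete the words *and safety*, so that the 21-day condition applies to the pharmacodynamic and efficacy assessments only. The Safety analysis section then governs safety for every randomised man with at least one dose or partial dose. The cost is the rewording of one sentence, with no new visits, data or analyses.
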